### Sample size calculations

Compliance: Compliance rates are expected to increase from 20% at baseline to 50% twelve months after the intervention. Assuming 120 observed opportunities for compliance per ward per measurement moment and a 10% heterogeneity between wards, a power of 93% was calculated with two-sided alpha = 0.05 for this design. In each hospital one ICU and one surgical ward will be included in the study.

Prevalence of HAI: 8568 patients are expected to be included in this study. Based on PREZIES data a baseline prevalence of HAI of 12% in the surgical ward and of 25% in the ICU is estimated [28]. Approximately 30% of these infections are exogenous and based on international literature a reduction of 40% of the exogenous part of these HAI can be expected in the intervention hospitals [29]. This will lead to a reduction in HAI in the surgical ward from 12-> 10%, and in the ICU from 25->22%. Based on an average reduction of 16-> 14% (when pooling the data) a power of 73% with a two-sided alpha = 0.05 was calculated. Since baseline measurements will be collected in all units this will enable comparison within units, substantially increasing the power.

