## Methods/Design

### Study design

The ACCOMPLISH package will be tested in a two-arm cluster randomized trial in 16 hospitals in the Netherlands (eight intervention and eight control) in one intensive care unit (ICU) and one surgical ward per hospital. In eight hospitals *ACCOMPLISH *will be introduced, while eight control hospitals will maintain normal HH practices. All infection prevention activities as well as any large outbreaks or other major events which might influence HH behaviour will be documented in a process evaluation. The primary outcome measure will be the observed hand hygiene compliance rate, measured at baseline (T1) and after 6 (T2), 12 (T3) and 18 (T4) months. As a secondary outcome measure the prevalence of HAI will be measured at the same time points. At each time point data identifying process indicators will be collected. The process evaluation will also include determinants of implementation, namely the social-political context, the organization, the adopting person (i.e. the HCW), the innovation itself and the facilities needed for implementation [13]. See figure 1 for an overview of the data collection activities.

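### The surgical-ward planning effect of 12 to 10% does not follow from the plan's stated assumptions, which give 10.6%; the HAI power rests on a slightly rounded-up pooled effect (about 70% unrounded, 73% printed)

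*Protocol article*

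**What the plan says.** All the figures stand in the second paragraph of the protocol article's section on sample size calculations.

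- Baseline: "a baseline prevalence of HAI of 12% in the surgical ward and of 25% in the ICU is estimated".
- Share that can respond: "Approximately 30% of these infections are exogenous".
- Expected effect on that share: "a reduction of 40% of the exogenous part of these HAI can be expected in the intervention hospitals".
- Resulting ward-type effects: "This will lead to a reduction in HAI in the surgical ward from 12-> 10%, and in the ICU from 25->22"%.
- Pooled effect and power: "Based on an average reduction of 16-> 14% (when pooling the data) a power of 73% with a two-sided alpha = 0.05 was calculated".
- Number of patients: "8568 patients are expected to be included in this study".

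The section on study design gives the allocation, "16 hospitals in the Netherlands (eight intervention and eight control"), and names HAI prevalence as a secondary outcome.

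**The concern.** The ward-type figures are presented as the consequence of the two assumptions before them, so a reader can check them within the paragraph. The ICU figure passes and the surgical-ward figure does not. As printed, the surgical ward has a larger relative effect than the ICU (2/12 = 16.7% against 3/25 = 12%), although the plan states one exogenous share and one preventable fraction for both.

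Two things are at stake. First, the printed expectation for the surgical ward is a 2-point fall where the assumptions support 1.44 points. Second, the HAI power should reflect the effect that the plan derives, and it is already below 80%. HAI prevalence is secondary, but it is also the third research question and the effect term in the cost-effectiveness ratio, so its planning figures should be right.

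**Working it through.** **Inputs.** From the section on sample size calculations: baseline 12% (surgical) and 25% (ICU), exogenous share 30%, prevented fraction of that share 40%, pooled 16 to 14%, 8568 patients, two-sided alpha 0.05, power 73%. From the section on study design: eight against eight hospitals. Assumption: patients divide equally, so n = 8568 / 2 = 4284 per arm.

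**Step 1. Reproduce the printed power.** Normal approximation for two proportions, pooled variance under the null, no design effect:

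power = Phi{ [ |p1 - p2| - 1.96 x sqrt(2 pbar (1 - pbar) / n) ] / sqrt( [p1(1 - p1) + p2(1 - p2)] / n ) }

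With p1 = 0.16, p2 = 0.14 and n = 4284, both standard errors are 0.00771. The argument is (0.0200 - 1.96 x 0.00771) / 0.00771 = 0.63, and power = 73.6%. With a continuity correction it is 72.7%. The printed 73% is therefore reproduced, and it comes from the pooled 16 against 14%.

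**Step 2. The effect that the assumptions imply.** Relative reduction = 0.30 x 0.40 = 0.12, so each prevalence is multiplied by 0.88.

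| | Baseline | x 0.88 | Printed | Agrees? |
|---|---|---|---|---|
| Surgical ward | 12% | 10.56% | 10% | No (rounds to 11%) |
| ICU | 25% | 22.00% | 22% | Yes, exactly |
| Pooled | 16% | 14.08% | 14% | Yes, after rounding |

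The printed surgical effect is 2.00 points and the derived effect 1.44 points, so the printed one is larger by 2.00 / 1.44 - 1 = 39%.

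**Step 3. Power at the unrounded pooled effect.** With p2 = 0.1408 and the same n, both standard errors are 0.00772. The argument is (0.0192 - 1.96 x 0.00772) / 0.00772 = 0.53, and power = 70.1% (69.0% with a continuity correction). Rounding 14.08 to 14 thus adds about 3.5 points.

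**Step 4. Sensitivity to the rounded baseline.** Keep the 12% relative reduction and let the pooled baseline be anything that prints as 16%. At 15.5% (to 13.64%) power is 68.4%; at 16.5% (to 14.52%) it is 71.6%. The range is 68 to 72%.

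**The case against.** The strongest defence is that every prevalence is printed as a whole percent and the exogenous share is only approximate. The printed figures can then all hold at once. With a share of 32%, the factor is 1 - 0.32 x 0.40 = 0.872, giving 10.46, 21.8 and 13.95%, which print as 10, 22 and 14. With the factor kept at 0.88, a surgical baseline of 11.9% gives 10.47%. The power shifts just as easily: a share of 29% gives 67%, 31% gives 73% and 32% gives 76%. This stands as far as it goes. It rules out saying that the figures cannot all be true, and it shows that 3.5 points of power lie within the imprecision of the inputs. It does not rescue the sentence as written. From the values that the plan prints, the surgical ward comes to 10.56%, and even where unrounded inputs bring it below 10.5% the expected fall is about 1.5 points, not 2.

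A reader might also infer stronger claims, which the document does not support:

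- *That the ward-type figures contradict the pooled 16 to 14%.* They do not. If the ward mix is solved from the pooled 16% (ICU share 4/13 = 31%), 10% and 22% pool to 13.69%, while 10.56% and 22% pool to 14.08%. Both print as 14%.
- *That the surgical-ward figure inflated the power.* It did not enter the calculation. Step 1 shows that the 73% comes from 16 against 14%; carrying 13.69% through would have given about 85%, which the plan neither prints nor uses.
- *That power for the surgical ward alone is at issue.* The plan states HAI power for the pooled comparison only.
- *That the ward mix is known.* It is only back-solved from rounded figures: a pooled baseline between 15.5 and 16.5% allows an ICU share of 27 to 35%.

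**Conclusion.** The concern holds in a narrow form. Taken as printed, the assumptions give 12 to 10.6% in the surgical ward, not 12 to 10%. The ICU figure is correct, and the pooled figure is correct after rounding. Separately from the surgical-ward figure, the power was taken at the rounded 14%; the effect as derived gives about 70% (68 to 72% over baselines that print as 16%) instead of 73 to 74%.

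This rests on reading 30% and 40% as stated, on equal numbers of patients per arm, and on the method that reproduces the printed power, which treats all 8568 patients as independent. That last feature is a separate question: randomisation is by hospital, and the printed power leaves almost no room for a design effect (4284 / 4219 = 1.015, where 4219 per arm gives 73% at 16 against 14%). It weighs more on this power than the rounding does.

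Severity is minor: one wrong intermediate figure and a small optimistic rounding, both for a secondary outcome. The primary outcome, the enrolment and the analysis are not touched.

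**What to change.** In the section on sample size calculations, print the expected effects as surgical ward 12 to 10.6%, ICU 25 to 22% and pooled 16 to 14.1%, and name the 12% relative reduction from which they follow. Restate the HAI power as about 70% on the printed method. If the power is restated to allow for clustering, carry the unrounded 16 against 14.08% into that calculation. If the authors worked from unrounded inputs (for example a share slightly above 30%), print those inputs instead, so that the figures can be reproduced.

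Do not add a 69/31 ward mix unless it comes from the planning data, since here it can only be back-solved. The cost is a change of wording and one recalculation, and the stated power becomes slightly less favourable. Enrolment and analysis stay as they are.

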### Selection of the sample

Randomisation will take place at hospital level by means of computer generation. Therefore in each hospital both wards will be included in the same arm of the trial.

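### The 73% power for healthcare associated infections has no allowance for hospital clustering, so it overstates what this design can deliver, and a gain from baseline data cannot be added on top of it

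*Protocol article*

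**What the plan says.** Protocol article, Sample size calculations, HAI paragraph:

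- Patients: "8568 patients are expected to be included in this study". No split by time point is given.
- Baseline rates: "a baseline prevalence of HAI of 12% in the surgical ward and of 25% in the ICU is estimated".
- Effect: about 30% of infections are taken as exogenous, and "a reduction of 40% of the exogenous part of these HAI can be expected in the intervention hospitals". By ward type: "This will lead to a reduction in HAI in the surgical ward from 12-> 10%, and in the ICU from 25->22" (per cent).
- Power: "Based on an average reduction of 16-> 14% (when pooling the data) a power of 73% with a two-sided alpha = 0.05 was calculated".
- Baseline data: "Since baseline measurements will be collected in all units this will enable comparison within units, substantially increasing the power".

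Elsewhere in the same article:

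- Selection of the sample: "Randomisation will take place at hospital level by means of computer generation", with both wards of a hospital in the same arm. Study design gives eight hospitals per arm.
- The compliance paragraph, just above the HAI one, includes 10% heterogeneity between wards. The HAI paragraph names no such allowance.
- HAI prevalence is measured at T1 (baseline), T2, T3 and T4, and Data analysis plans a multilevel model.

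**The concern.** When hospitals are randomised, patients in the same hospital are not independent. With several hundred patients per hospital, even a very small ICC removes much of the information. A power figure that leaves this out describes a different trial. An analysis plan that is not shown cannot change how the published 73% was obtained.

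HAI is a secondary outcome, so the primary comparison is not affected. The figure still matters. The Discussion presents this as the first randomised trial of a hand hygiene programme on the number of infections, and the Economic Evaluation divides net costs by the HAI difference. A reader who is told 73%, and substantially more with baseline data, could take a non-significant HAI result as evidence against the package, when such a result would be likely at modest ICCs even if the assumed effect were real.

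**Working it through.** **Inputs from the protocol article.** 8568 patients, 16 hospitals (8 v 8), rates 16% v 14%, two-sided alpha 0.05, four measurement points. **Assumed.** ICC for HAI (none is stated), equal hospital sizes and, where indicated, 8568 spread evenly over T1-T4.

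**1. Reproducing 73%.** With n = 8568/2 = 4284 per arm and design effect 1:

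SE = √[(0.16×0.84 + 0.14×0.86)/4284] = √(0.2548/4284) = 0.00771

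z = 0.02/0.00771 = 2.593; power = Φ(2.593 − 1.960) = 73.7%

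The pooled-variance form gives 73.6% and the continuity-corrected form 72.7%. Variants that do not match: one-sided 82.8%; 8568 per arm 95.6%; three quarters of the patients 61.2%. The stated figure therefore uses all 8568 patients with no clustering allowance.

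**2. Adding hospital clustering, no baseline adjustment.** Design effect DE = 1 + (m − 1)×ICC, with m patients per hospital; effective n per arm = n/DE. If 8568 spans T1-T4 evenly, the follow-up patients number 0.75×8568 = 6426 (3213 per arm, m = 401.6). If all 8568 are follow-up patients, m = 535.5. Power is shown as normal test / t test on 14 df.

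| ICC (assumed) | DE, m = 401.6 | Power, 6426 follow-up | DE, m = 535.5 | Power, 8568 follow-up |
|---|---|---|---|---|
| 0 | 1.00 | 61.2% / 55.2% | 1.00 | 73.6% / 67.5% |
| 0.001 | 1.40 | 47.5% / 42.4% | 1.53 | 55.3% / 49.6% |
| 0.002 | 1.80 | 38.7% / 34.4% | 2.07 | 43.7% / 39.0% |
| 0.005 | 3.00 | 25.3% / 22.6% | 3.67 | 27.2% / 24.2% |
| 0.01 | 5.01 | 16.9% / 15.3% | 6.35 | 17.6% / 15.9% |

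**3. What baseline data can add.** Take m0 = 8568/64 = 133.9 patients per hospital at T1 and m1 = 401.6 at T2-T4, σ² = 0.15×0.85 = 0.1275, and a hospital effect that is fully stable over time. With b = ICC×σ²:

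- V0 = b + (1 − ICC)σ²/m0 and V1 = b + (1 − ICC)σ²/m1
- Variance per hospital: follow-up only V1; change score V0 + V1 − 2b; ANCOVA V1 − b²/V0
- SE of the arm difference = √(2×variance/8)

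At ICC 0.005: b = 0.000638, V0 = 0.001585, V1 = 0.000953. The SEs are 0.01544 (follow-up only), 0.01777 (change score) and 0.01320 (ANCOVA). Power by t test on 14 df (13 df lowers it by about half a point or less):

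| ICC (assumed) | Follow-up only | ANCOVA on T1 | Raw change score |
|---|---|---|---|
| 0.001 | 42.3% | 43.5% | 18.1% |
| 0.002 | 34.4% | 37.4% | 18.1% |
| 0.005 | 22.6% | 29.2% | 18.1% |
| 0.01 | 15.3% | 24.6% | 18.2% |
| 0.02 | 10.3% | 21.8% | 18.3% |

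The flat change-score figure depends on the stable hospital effect. With a correlation of 0.8 between the baseline and follow-up hospital effects and ICC 0.01, it falls to 14.2%, and ANCOVA to 19.9%.

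**4. The case most favourable to the plan.** Let all 8568 be follow-up patients, add a further baseline round one third that size, and keep the hospital effect fully stable. ANCOVA then gives 73.6% (normal) or 67% (t) at ICC 0, and by t test 51% at 0.001 and 34% at 0.005. It does not exceed the 73% already claimed. Adjustment works by removing between-hospital variance, and the 73% contains none.

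**5. The effect assumption.** 0.30×0.40 = 12% relative reduction: 12% × 0.88 = 10.56%, 25% × 0.88 = 22.0%, 16% × 0.88 = 14.08%. The ICU figure is exact, and the pooled 14% is correct to the nearest per cent. The surgical ward figure should be 10.6%, not 10%. Putting 14.08% into step 1 gives 70.1%.

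**The case against.** The strongest reply is that HAI is secondary, that 73% is already below the customary 80%, and that the planned multilevel analysis would protect the inference whatever the power paragraph says. That stands as a limit on how serious this is. It does not make the 73% correct for a trial that randomises hospitals.

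Several stronger readings are tempting, and the document does not support them:

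- *Comparison within units reduces power.* This is true of a raw change score at low ICC, but the protocol does not specify one. Once clustering is modelled, ANCOVA on baseline raises power at every positive ICC in step 3, and at ICC 0.01 with a stable hospital effect even the change score beats follow-up only (18.2% v 15.3%). The statement about baseline data is right in direction. Its fault is that the gain is unquantified and is placed on top of an unclustered figure.
- *Baseline patients are counted in the comparison.* This is plausible, since the 8568 are described as included in the study and T1 is one of four measurements, but no split is given. The clustering problem holds either way.
- *The design has one particular low power.* Any single figure or narrow band rests on an ICC that the document does not state.
- *The rounding from 10.6% to 10% inflates the 73%.* It does not enter that calculation. The pooled 16% implies an ICU share of (16 − 12)/(25 − 12) = 31%; the rounded ward figures would then give a pooled drop of 0.69×2 + 0.31×3 = 2.3 points, and the protocol used the smaller 2 points.

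**Conclusion.** The point holds in this form. The stated HAI power is that of an individually randomised trial with design effect 1 and overstates the power of this one. How far depends on the unstated ICC: for an unadjusted comparison, about 42-55% at 0.001, 23-27% at 0.005 and 15-18% at 0.01, across both readings of the 8568 and both tests. If the 8568 include T1 patients in equal quarters, power is about 61% by normal test even with no clustering. Baseline adjustment recovers part of the loss (23% to 29% at ICC 0.005, even spread over T1-T4), but under the model used here it does not exceed 73%, so the claimed substantial increase cannot be added to that number.

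The reproduction of 73% and the absence of a clustering allowance are firm. The replacement figures are conditional on assumed ICCs, equal hospital sizes and, for baseline adjustment, a stable hospital effect.

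**What to change.** In the HAI paragraph of Sample size calculations:

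1. Restate the power at hospital level (8 v 8) over a stated ICC range, using post-baseline patients.
2. Say which time points the 8568 patients cover.
3. Replace the claim of a substantial power increase with a baseline-adjusted figure from the same clustered calculation, or remove it as an addition to 73%.
4. Correct the surgical ward reduction to 12% -> 10.6%. This is minor and does not feed the 73%.

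The cost is wording and a less favourable stated figure for a secondary outcome. No extra patients, hospitals or measurements are needed.

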### Selection of the sample

Randomisation will take place at hospital level by means of computer generation. Therefore in each hospital both wards will be included in the same arm of the trial.

### Data analysis

Process indicator questionnaires: These will be analysed with multivariable linear regression analysis, with self-reported compliance (never-always on a 10-point scale) as primary outcome variable. The determinants included in the questionnaire will include the socio-political context, the organization, the adopting person or HCW, the innovation and the facilities needed to implement the innovation [13]. Furthermore behavioural determinants will be included in the questionnaire, including attitudes, social norms, perceived behavioural control, intention, habit, knowledge of the guidelines and patient safety culture (as measured by the ComPaz questionnaire) [30].

Randomised controlled trial: The effect of the intervention strategy on the overall compliance rate among HCW (logistic regression analysis), and on prevalence of HAI will be assessed. Multilevel analysis will be performed to compensate for the clustered nature of the data (HCW are clustered within wards), using mixed linear modelling techniques.

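### The compliance model names only healthcare workers within wards as clustering, so an effect estimated against T1 would reject above 5% if wards fluctuate between measurement rounds

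*Protocol article*

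**What the plan says.** The article describes the analysis of the randomised comparison in two sentences of the Data analysis section. The first is "The effect of the intervention strategy on the overall compliance rate among HCW (logistic regression analysis), and on prevalence of HAI will be assessed". The second is "Multilevel analysis will be performed to compensate for the clustered nature of the data (HCW are clustered within wards), using mixed linear modelling techniques".

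The design has more structure than that parenthesis. Under Study design, compliance is "measured at baseline (T1) and after 6 (T2), 12 (T3) and 18 (T4) months", and the hospitals are split as "eight intervention and eight control) in one intensive care unit (ICU) and one surgical ward per hospital". That makes 16 wards per arm and 32 in all, each measured four times. Under Selection of the sample, "Randomisation will take place at hospital level by means of computer generation". Sample size calculations gives the planning figures for compliance: "Compliance rates are expected to increase from 20% at baseline to 50% twelve months after the intervention" and "Assuming 120 observed opportunities for compliance per ward per measurement moment", with 10% heterogeneity between wards, two-sided alpha of 0.05 and 93% power.

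The article names no repeated-measurement, ward-by-time or hospital term. It does not say whether the primary test is a difference in change or a difference at follow-up.

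**The concern.** A ward intercept assumes that two opportunities in the same ward are equally correlated whether they fall in the same round or 18 months apart. Real wards move between rounds. The article itself expects this: it averages two prevalence measurements per time point to smooth out variation, it records outbreaks and other disturbing events, and it collects staffing ratio and patient numbers as influences on hand hygiene.

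If the model has no term for such movement, the movement is divided by 120 opportunities as though it were binomial noise. Any contrast that sets follow-up against T1 removes the stable ward level and leaves the unmodelled movement in the estimate. Its standard error is then too small. What is at stake is the primary outcome: a chance difference in drift between eight and eight hospitals could be reported as an effect of the programme. Adding a hospital intercept alone would not cure this, because that intercept is also constant over time.

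**Working it through.** **Inputs from the article.** 8 + 8 hospitals, 2 wards each, 4 rounds, m = 120 opportunities per ward and round, compliance 20% to 50%, 10% heterogeneity, alpha 0.05 two-sided.

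**Assumptions.** The 10% heterogeneity is read as ICC = 0.10; the article does not give its scale. The correlation r of a ward's true level between rounds is not given, so a range is used. Cluster sizes are equal.

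**The stated power.** Design effect 1 + 119 × 0.10 = 12.9. With 8 clusters per arm, effective n = 8 × 120 / 12.9 = 74.4. The standardised difference is 0.30 / √(2 × 0.35 × 0.65 / 74.4) = 3.84, and the noncentral t on 14 df gives 94.5%, close to the stated 93%. With 16 independent wards per arm the same calculation gives about 99.9%. The stated figure therefore fits inference on about 8 units per arm better than on 16 wards. The article does not say how it was obtained.

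**Ward intercept only, change from T1.** In units of p(1 − p), the model gives a ward-round mean a conditional variance of (1 − ICC)/m = 0.9/120 = 0.0075. The true value adds ICC × (1 − r). The variance ratio is

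VIF = 1 + m × ICC × (1 − r) / (1 − ICC), and type I error = 2 × [1 − Φ(1.96/√VIF)].

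| r | VIF | Type I error |
|---|---|---|
| 1.00 | 1.00 | 5.0% |
| 0.95 | 1 + 0.6/0.9 = 1.67 | 12.9% |
| 0.90 | 1 + 1.2/0.9 = 2.33 | 19.9% |
| 0.80 | 1 + 2.4/0.9 = 3.67 | 30.6% |

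A model that constrains the T1 mean to be equal in both arms gives nearly the same: about 13%, 19% and 30% at r = 0.95, 0.90 and 0.80. If the heterogeneity is instead a between-ward SD of 0.10 at 20% compliance, ICC = 0.01/0.16 = 0.0625, and the change test gives 9.8%, 14.4% and 22.4%.

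**Simulation of the change test.** No arm effect, 32 wards, 4 rounds, compliance 20% at T1 and 25% later in both arms, ICC 0.10 on the logit scale, logistic model with a ward intercept, 1,200 runs per setting. The arm-by-T3 test rejects 4.9%, 10.2%, 13.3% and 22.7% at r = 1, 0.95, 0.90 and 0.80. The joint arm-by-time test rejects 5.6%, 13.8%, 23.8% and 38.9%. These figures lie below the closed form because a logit-scale ICC of 0.10 is smaller on the proportion scale: the latent variance is (0.1/0.9) × π²/3 = 0.366, and multiplied by p(1− p) of 0.16 to 0.19 this is about 0.06 to 0.07.

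**Healthcare-worker effects fitted as well.** Take H workers per ward and round, different workers each round, and worker ICC s. Let w = 0.10 × (1 − r), e = 0.90 − s and f = 3H/(4H − 1). The true variance is w + s/H + e/120, and the modelled variance is (f·w + s)/H + e/120. Type I error = 2 × [1 − Φ(1.96 × √(modelled/true))].

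- H = 6, s = 0.10, r = 0.95: 0.02399/0.02833 = 0.847, giving 7.1%.
- H = 24, s = 0.05, r = 0.95: 0.00932/0.01417 = 0.658, giving 11.2%.
- H = 6, s = 0.10, r = 0.80: 0.02594/0.04333 = 0.599, giving 12.9%.
- H = 24, s = 0.05, r = 0.80: 0.00980/0.02917 = 0.336, giving 25.6%.

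**Follow-up contrast from the ward-intercept model.** The stable ward level stays in the variance and dominates it. In closed form with ICC 0.10, an arm difference at T3 has a type I error of 5.4% to 6.9% for r from 0.95 to 0.80. In the simulation the average follow-up contrast rejects 6.3% to 6.8% over the same range.

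**Movement carried in the error.** In the simulation, a t-test on each ward's logit change from T1 to T3 rejects 3.6% to 5.8% for r from 0.50 to 1. In a separate simulation with two rounds and hospital effects, a t-test on hospital-level change (14 df) rejects 4.3% to 5.6%.

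**The case against.** The strongest reply is that this is a condensed article. The parenthesis illustrates clustering without excluding other levels, and a fuller plan may add them. That has weight and lowers the severity. It does not dispose of the point, because the article chose to state the structure, and the one it states fits neither the repeated measurement nor the unit of randomisation.

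Three further objections stand in part.

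- **The contrast is not fixed.** The article speaks of an effect on the overall compliance rate and names no change test. A reader might infer that compliance will be tested as change within wards, because baseline data are said to matter: "this will enable comparison within units, substantially increasing the power". That sentence is in the infection paragraph, and nothing like it is said for compliance. The inflation is therefore conditional on T1 being used, which is usual when a baseline is collected but is not stated here.
- **The size is not known.** A reader might infer that the test rejects grossly too often. The article gives no ward-by-time variance, and modelling worker effects absorbs part of the excess. At a between-round correlation of 0.95 with worker effects, the error is only 7% to 11%. The article also does not say whether the same staff are observed in each round.
- **Infection prevalence.** A reader might extend the fault to the secondary outcome. The article averages two point-prevalence measurements per time point and refers to linear mixed models. If averaged unit prevalences are analysed, the residual already contains the unit-by-time fluctuation, so no fault is shown there.

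**Conclusion.** The point holds in conditional form, and for compliance. The clustering named in the article is incomplete for 32 wards measured four times in 16 randomised hospitals. Fitted as named to opportunity-level data, with an effect estimated against T1, it gives intervals that are too narrow for any positive ward-by-time variance. With ICC 0.10 and between-round correlations of 0.95 to 0.80, the type I error is about 13% to 30% without worker effects and about 7% to 26% with 6 to 24 workers per ward and round and a worker ICC of 0.05 to 0.10. These inputs are assumptions. The direction does not depend on them, since the error is nominal only if wards do not move at all.

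A comparison at follow-up alone is little affected by this omission. That figure comes from calculations without a separate hospital effect, so it does not show that leaving out the hospital level is harmless. This should be corrected before analysis, but it falls short of a fatal fault, because the article fixes neither the contrast nor the variance.

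**What to change.** In the Data analysis section, replace the parenthesis with a statement of the full structure and name the primary contrast, including the time point. Either of two forms will do for compliance.

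1. Calculate one compliance summary per hospital per round. Compare follow-up between arms with the hospital's T1 value as covariate, with inference on 16 hospitals (16 − 3 = 13 df for a single follow-up value with intercept, arm and T1).
2. Keep the opportunity-level logistic model, but add hospital and ward intercepts and cluster-by-time random effects, with small-sample degrees of freedom that reflect 16 hospitals.

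For infection prevalence, it is enough to state whether averaged unit prevalences or individual patients are analysed. If patients are analysed, the same structure should be used.

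The cost is a few sentences and no new data. Standard errors become wider, and correct. The stated 93% power is already close to what 8 clusters per arm give, so inference on hospitals does not contradict the planning figure.
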